## Discussion

NSSI is above all a high-risk marker for the development and persistence of mental health problems, encompassing high rates of morbidity and mortality and causing substantial costs for the health system. It is a common and highly recurrent behavior that peaks in adolescence [11, 12], and has been reported to be the fifth most frequent health risk in adolescence [1]. There is an urgent need to counter these developments and potentially tragic long-term consequences for young adolescents. What we do know is that targeted approaches significantly reduce NSSI and improve mental health, but access to such approaches is limited due to a lack of resources and specially trained physicians. A universal prevention program may help to overcome this matter and ensure an exhaustive protection to counteract this problem of epidemic proportions. However, so far, only one uncontrolled study (SOSI) has examined the effects of a universal prevention program for young adolescents [18] and on study examined the efficacy via a randomized controlled trial with a pre-post design [17]. Thus, this is the first RCT to develop and evaluate a universal prevention program with follow-up measurements to prevent NSSI. The present study, and especially DUDE, entails several advantages compared to previous work. First, we have consciously chosen not to employ any psychoeducational elements, as these have triggered iatrogenic effects in other universal prevention programs [24, 67]. Second, we provide a program addressing emotion regulation in accordance with effective psychotherapy (e.g., DBT) or targeted prevention programs (e.g., “cutting down”) in the field of reducing NSSI and suicidality over the emotional pathway. A third advantage is the implementation of DUDE in schools. On the one hand, adolescents spend most of their time at school and have to use emotion regulation skills on a regular basis. This facilitates the transfer to the students’ real life. On the other hand, as the school setting is capable of providing training for everybody, a large number of pupils can benefit, and most importantly, no stigmatization of the affected adolescents will occur. Fourth, bullying, as an important risk factor for mental health problems [68], is also addressed in DUDE by interactive exercises. This promotes cohesion within the group and strengthens solidarity.

### Limitations

Despite the mentioned advantages, potential limitations of the study design should be acknowledged. First, in accordance with the Ministry of Education and Cultural Affairs, to maximize practicability, we have chosen a cluster (school-wise) randomization procedure, which is common and recommended in the study of school-based prevention programs [25, 69, 70]. Nevertheless, this randomization procedure differs from other studies, and especially psychotherapeutic studies, which randomize participants by subject or class. We will seek to protect the study from contamination through the randomization procedure. Randomizing at the school level ensures that participants, and particularly those from the control conditions, are unable to obtain material or information covered in the prevention condition due to contact with each other [69]. Second, we are trying to standardize the implementation of DUDE in the treatment groups through training and the manual such that high manual fidelity can be ensured. However, we are aware that in treatment group 2, teachers are unlikely to adhere to our manual 100% due to their many daily responsibilities. This will potentially have an impact on the efficacy of our program. We will attempt to monitor standardized implementation with measures of adherence (see the “Process and adherence variables” section) after each lesson, as in psychotherapy studies. However, it is not certain that this will work. It is important to determine if there are group differences between the different trainers (clinical psychologists vs. teachers) in the implementation of DUDE, as this could affect the efficacy of the program. Ultimately, the implementation of DUDE by teachers is hugely important for subsequent dissemination. Third, we must ask whether DUDE is superior to targeted prevention, because universal prevention usually achieves low effect sizes. Perhaps it would make more sense to identify pupils with high-risk or emerging self-injurious behavior using a brief questionnaire and refer them to targeted interventions that have already been shown to be effective. However, the problem with this procedure is that disclosure of psychopathological behavior in the school setting may still lead to stigmatization of affected students. Fourth, our findings must take into account the SARS-Covid-19 pandemic and its impact on pupils’ mental health. If the pandemic-related conditions that led to psychological and behavioral problems among adolescents are reversed and a “normal” daily routine is possible again, this could also lead to an improvement in mental health and be falsely associated with the efficacy of DUDE. However, the randomized controlled trial design should prevent such misconceptions, and the additional measurement of SARS-Covid-19 burdens (see the “Confounding variables” section) should control for the influence of this factor on efficacy. Nevertheless, due to the current pandemic-related high mental stress and decreased quality of life among children and adolescents, we believe it is imperative to implement universal prevention programs to improve emotion regulation and reduce maladaptive behaviors in order to help those affected and actively contribute to improving the current situation for young people.

DUDE is tailored to diminish the incidence of NSSI and prevent adolescents from the possible long-term consequences thereof (e.g., suicidality). It provides easy access for adolescents due to its implementation in a school environment and is cost-effective. Furthermore, DUDE is a comprehensive approach which tries to improve mental health through the pathway of improved emotion regulation.

### Trial status

Protocol version 2, 27 June 2020. The trial is scheduled to be completed on May 2023 with T3. Recruitment will begin in October 2021 and recruitment will be completed in April 2022. https://www.drks.de/drks_web/navigate.do?navigationId=trial.HTML&TRIAL_ID=DRKS00018945

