## Methods/design

### Setting and recruitment

The present trial is a study from the newly founded German Centre of Prevention Research in Mental Health at the University of Wuerzburg in Germany. The aim of this center is to develop and implement existing prevention programs, evaluate their efficacy and effectiveness, and ensure their sustainability and broad dissemination.

In the present trial, we aim to include *N* = 3200 young adolescents (age 11–14 years) in Germany within a school-based setting with 16 schools. There are several reasons why the school setting is ideally suited for this trial: (1) First of all, NSSI is a phenomenon with epidemic proportions. Based on the high prevalence and the possible outcomes of NSSI, a school-based setting and population is reasonable in terms of universal prevention. (2) As mentioned, there is a need to further develop and evaluate universal prevention in the field of NSSI (see the “Background” section). (3) Targeted trials entail a selection bias, meaning that access is often limited to the location where the targeted prevention is implemented (mostly universities or clinics). Furthermore, adolescents will not be stigmatized during the allocation process. Hence, even if adolescents are suffering and undergoing emotional struggles but are afraid or reluctant to ask for help, they will eventually benefit from the participation in DUDE. Therefore, their risk of developing mental health problems in general, and engagement in NSSI in particular, might be decreased.

The recruitment of the 16 schools will occur in collaboration with the Bavarian Ministry of Education and Cultural Affairs. First, the schools will be selected at random by a staff member of the Ministry. Following this, the schools will be randomly assigned (cluster randomization) to the treatment group (1 or 2) or to the active control group using cluster randomization by an assigned external researcher who is not part of the study group. All eligible pupils of the participating schools will be offered the chance to participate in the study. The assessment time points of the study are before the start of treatment (baseline, T0), at the end of the treatment (T1), 6 months after the end of treatment (T2), and 12 months after the end of treatment (T3) in order to evaluate the efficacy of the universal prevention. The flow chart of the trial is shown in Fig. 1 and the trial schedule is depicted in Fig. 2.

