After the feasibility stage, the main study will start. First of all, the schools for the main study will be chosen by the Ministry of Education and Cultural Affairs. The respective school principals will then be contacted to ensure that the implementation of the study will run smoothly. This will be followed by a personal meeting with the teaching staff and the study team to inform about the rationale, aims, and study procedure. At this point, schools will not yet have been randomly assigned to a trial group. This should prevent any bias due to motivational effects during the recruitment. Once schools have given consent, pupils and parents will receive information about the study in the following order: (1) An information evening (1 ½ h) about the study will be held for parents and pupils. (2) Subsequently, parents and participants will once again receive all information in writing and the consent form via mail or e-mail. (3) To give the participants another opportunity to ask questions, information about the study will be provided again (during a regular lesson) before data collection, and the presence of the consent forms will be checked. The written and oral information will include the following: background and objectives of the study, information about the prevention program (DUDE) and minimal intervention, benefits and possible risks of participation, data collection procedures, and data security procedures. After parents and adolescents have received the required information, informed consent will be obtained. The parents and participants will confirm with their signature that they have read and understood the provided information and that they are willing to participate. Nevertheless, they will be able to withdraw from the study at any time without any consequences for subsequent school matters or medical care (see also the “Ethical issues and dissemination” section). Next, schools will be randomized. Before the baseline measurement, pupils will be checked for eligibility and the booklets (“Stress-free through the school day”) will be handed out. Seven days (± 3 days) after the baseline measurement, DUDE will conducted in treatment groups 1 and 2 and will be integrated into the normal school schedule.

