Given the very large number of over 3000 participants, the measurements and execution of DUDE will be split into two time points. We aim to begin in November 2021, and the second round of assessment should take place around March 2022. However, due to the SARS-Covid-19 pandemic, delays are possible. To ensure that enough individual pupils give their consent to participate, the DUDE training will be integrated into the regular school day, during lesson time, to make participation more attractive to the students.

As mentioned above, to prevent bias, 16 schools will be randomly (cluster randomization, see the “Discussion” section) assigned to DUDE or to the active control group, with eight schools per group, using cluster randomization. Within the treatment group, there will be a secondary randomization into treatment groups 1 or 2. Enrolment, generation of allocation sequence, and assignment of schools will be carried out using the software SAS by an independent member of the institute not involved in the project. The schools will be informed about their group affiliation via e-mail and telephone call immediately after randomization. Nevertheless, blinding is not completely possible, as schools cannot be blinded to the different nature of the interventions. Blinding of the researchers is also not possible because the treatment group will receive DUDE in addition to the minimal intervention.

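### The article does not settle whether pupils consent before or after their school's arm is known, and the two-round calendar leaves second-round consent exposed unless each round is randomised separately in whole schools

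*Protocol article*

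**What the plan says.** *Procedure and randomization* sets out a sequence. School staff are informed first, and "At this point, schools will not yet have been randomly assigned to a trial group"; the stated reason is to avoid motivational bias in recruitment. Parents and pupils are then informed and sign consent. Only after that: "Next, schools will be randomized".

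*Setting and recruitment* tells it in another order. The Ministry selects schools. Then "Following this, the schools will be randomly assigned (cluster randomization) to the treatment group (1 or 2) or to the active control group", and the sentence after that reads "All eligible pupils of the participating schools will be offered the chance to participate in the study". *Inclusion and exclusion criteria* likewise describes the pupils approached as those of schools already assigned.

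On timing, *Procedure and randomization* says that "the measurements and execution of DUDE will be split into two time points" and adds: "We aim to begin in November 2021, and the second round of assessment should take place around March 2022". It warns that the pandemic may cause delay. It describes the allocation as 16 schools, eight per group, with a second randomisation inside the treatment group, and states: "The schools will be informed about their group affiliation via e-mail and telephone call immediately after randomization". *Data assessment* puts baseline (T0) after randomisation. *Trial status* says "Recruitment will begin in October 2021 and recruitment will be completed in April 2022", with the last T3 in May 2023.

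**The concern.** Consent before allocation is the safeguard the authors chose, and it matters here because neither schools nor researchers are blinded. If families decide once the arm is known, different kinds of pupils may join in the two arms: one offers five 90-minute training units in lesson time, the other a booklet. The authors themselves expect that placing DUDE in lesson time will make pupils more willing to take part.

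Randomising schools does not protect against this, because the selection happens after randomisation and within schools. The planned intention-to-treat analysis and multiple imputation do not repair it either. Both act on enrolled pupils, and those who never consented are not in the data.

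**Working it through.** **1. Order of consent and allocation**

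- *Procedure and randomization*: school consent, family information, family consent, randomisation, eligibility check, baseline.
- *Setting and recruitment*: school selection, randomisation, offer to pupils.
- *Inclusion and exclusion criteria*: pupils of assigned schools are asked.

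The first gives an explicit sequence. The other two read the opposite way, though less firmly: the sentence on the offer has no time word, and assigned could mean assigned to the study.

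**2. The plan's own end date**

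Inputs: T0 is 7 days before DUDE starts (*Data assessment*); five weekly units, so 4 to 5 weeks (*DUDE*); T3 is 12 months after the end of DUDE.

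- Round 1, T0 from 1 to 30 November 2021: DUDE ends between 6 December 2021 and 11 January 2022, and T3 falls between 6 December 2022 and 11 January 2023.
- Round 2, T0 from 1 to 31 March 2022: DUDE ends between 5 April and 12 May 2022, and T3 falls between 5 April and 12 May 2023. This reproduces completion in May 2023.
- Backwards from T3 in May 2023: DUDE ends in May 2022, starts between about 3 April and 3 May, and T0 falls between about 20 March and 26 April 2022.

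Recruitment to April 2022 therefore fits a second round that slips a little past March.

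**3. What the dates imply under each unstated design**

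- *One allocation of all 16 schools.* T0 follows randomisation, so the allocation precedes the November 2021 baseline and is disclosed at once. Consent given in April 2022 comes about five months later (November to April).
- *Per-round randomisation, whole schools, after that round's consent.* Consent always precedes disclosure, and every stated date can be kept.
- *Per-round randomisation, rounds split within schools.* Each school supplies 6th and 7th grade (*Sample size*), so such a split is possible. The school's arm is then known from its first round, and its second-round families consent with that knowledge.

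The text splits measurement and delivery into rounds. It does not say that consent or randomisation is split.

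**4. Illustration of size (assumptions, not data)**

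Assume equal rounds (1600 of 3200 pupils each), no true effect, a new-case rate of 2.31% (*Sample size*: 5.31 − 3.00), and selection in round 2 only. Let *r* be the enrolment of future cases in control schools relative to DUDE schools, with other pupils enrolling equally. Cases are rare, so approximately:

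spurious difference = 0.5 × 2.31 × (1 − *r*) percentage points

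- *r* = 0.9: 0.5 × 2.31 × 0.10 = 0.12, or 5% of the planned 2.31
- *r* = 0.75: 0.5 × 2.31 × 0.25 = 0.29, or 12.5%
- *r* = 0.5: 0.5 × 2.31 × 0.50 = 0.58, or 25%

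The sign reverses if future cases enrol less readily in DUDE schools. Under the second design in step 3 this source of bias is absent.

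**The case against.** The case on the other side is substantial. No sentence dates the allocation of all 16 schools before November 2021; the article gives counts, not a date or a number of steps. The dedicated section states the protective order plainly, and applying it round by round satisfies every date. The word recruitment under *Trial status* may refer to schools, as it does in *Setting and recruitment*. That section is an overview, and its sentence order may be only narrative. The article also cites a protocol version that is not shown, where release of allocations and closing of consent lists may be described.

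Most of this stands. A reader might infer that the safeguard and the calendar are incompatible, or that pupils will join after allocation or even after their school's baseline. The documents support neither. Whole-school rounds randomised after their own consent reconcile the dates, April 2022 fits the second round, and consent forms are to be checked before data collection.

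Two things remain. The reconciling design is nowhere stated, and the natural reading of one 8:8 allocation disclosed at once points the other way. And this is not simply detail left to a fuller document: the article does give the order of consent and allocation, and gives it inconsistently.

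**Conclusion.** The point holds as an inconsistency with a real bias risk behind it, not as a proven breach. *Procedure and randomization* puts consent before randomisation; *Setting and recruitment* and *Inclusion and exclusion criteria* describe the approach to pupils after assignment. Given immediate disclosure, two rounds and recruitment to April 2022, the safeguard is secure only if randomisation is done per round in whole schools after that round's consent, or if second-round allocations are withheld until then. Neither is stated.

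If neither is done, second-round families could consent up to about five months after disclosure. The number of pupils affected and the size and direction of any bias are unknown; 1600 pupils and 0.12 to 0.58 points rest wholly on the assumed equal rounds and enrolment ratios. No sample size or power figure changes. The change should still be made, because it costs little and the bias cannot be repaired after enrolment.

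**What to change.** - Assign whole schools to a round.
- For each round, lock the list of consenting pupils in all its schools before any of them is randomised or told its arm. Either randomise round by round, or have the independent operator withhold second-round allocations until those lists are locked.
- Base the primary analysis on the pupils on the locked lists, subject to the eligibility criteria already stated.
- Align the text: put the offer to pupils before assignment in *Setting and recruitment* and *Inclusion and exclusion criteria*; say in *Procedure and randomization* whether randomisation is single or per round; give in *Trial status* a consent closing date per round that precedes that round's disclosure.

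The cost is protocol wording and the timing of the allocation notice. Second-round schools learn their arm later, which shortens their preparation time, and pupils who consent late take part without being analysed.

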## Data Availability

Not applicable.

## Abbreviations

BDSG: Bundesdatenschutzgesetz
CBT: Cognitive Behavioral Therapy
DBT: Dialectical Behavior Therapy
DERS-SF: Difficulties in Emotion Regulation Scale- Short Form
DSHI-9: Deliberate Self-Harm Inventory - 9 items
DRKS: Deutsches Register für Klinische Studien
DUDE: Du Und Deine Emotionen
EU-DSGVO: Europäische Datenschutzgrundverordnung
FAS III: Family Affluence Scale III
FEVER: Fragebogen zur Erfassung der Veränderungsbereitschaft
ICC: Intraclass correlation coefficient
ITT: Intention-to-treat
LDSG: Landesdatenschutzgesetz
NSSI: Non-suicidal self-injury
PSS: Paykel Suicide Scale
PHQ-9: Patient Health Questionnaire- 9-item version
RCT: cluster-randomized controlled trial
REDCap: Research Electronic Data Capture
RESE-R: Regulatory Self-Efficacy Scale
RKI: Robert Koch Institute
SARS: Severe Acute Respiratory Syndrome
SDQ: Strengths and Difficulties Questionnaire
SEED: Short Evaluation of Eating Disorders
SEYLE: Saving and Empowering Young Lives in Europe
SOSI: Signs of self-injury
STAR: Self-injury: Treatment, Assessment, Recovery
URICA: University of Rhode Island Change Assessment
WHO: World Health Organization
